## Background {6a}

The prevalence of obesity in pregnant women in England at the time of booking a caesarean section (CS) has been reported to be 16% [1, 2]. One complication of obesity in pregnancy relates to the requirement for operative delivery, i.e. CS. The rate of CS in an obese (Body Mass Index BMI ≥ 30 kg/m^2^) pregnant population is 33.8% [3]. The rate of post-CS infection is higher amongst obese pregnant women compared to those who are not obese; the adjusted odds ratio of surgical site infection in an obese population was reported to be 2.41 (95% CI 1.73–3.37) [4]. Prophylactic single dose perioperative intravenous (IV) antibiotic is recommended for CS; and several studies have examined the use of alternative antibiotics, with cefazolin being the most commonly used in the USA and cefuroxime in the UK. Numerous studies have focussed on the use of cefazolin in obese patients undergoing CS to gain an understanding of optimal dosing and clinical outcomes [5]. Several studies proposed an increased dose of cefazolin (3 g) compared to the standard dose (2 g) for obese pregnant women to achieve sufficient antibiotic levels during CS [6–8]. It was postulated by Holt et al. (in 1994) that doses of cefuroxime up to 1500 mg may not achieve sufficient minimum inhibitory concentration (MIC) for most of the common bacteria in maternal blood during CS [9]. Sub-therapeutic antibiotic concentration is a crucial factor in global bacterial resistance. It is essential that the therapeutic concentration of antibiotic is achieved in both maternal blood and at the site of incision during CS for effective therapy. No study to date has measured cefuroxime concentrations in blood and adipose tissue in obese pregnant women undergoing CS [10]. Thus, a study to explore the drug concentration in this population at the time of CS is essential. This study will analyse cefuroxime concentration in plasma and adipose tissue samples to accurately measure levels achieved in non-obese and obese pregnant women undergoing CS to confirm if therapeutical cefuroxime levels are reached in plasma and adipose tissue. Further, to use the measured cefuroxime concentrations to verify a physiologically based pharmacokinetic (PBPK) model of cefuroxime in CS to explore the impact of (i) dose and (ii) BMI post-administration of cefuroxime on both blood and tissue cefuroxime concentrations in an obese population and suggest a dose adjustment if required and applicable.

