### Objectives {7}

The main objective of conducting this pilot and feasibility study is to assess the process and protocol of recruiting patients, sample collection, follow-up and procedure of C-LACE. Also to gain an understanding of cefuroxime concentrations in normal-body weight pregnant vs. obese pregnant women. The primary objective is to measure the concentration of cefuroxime in the collected blood and tissue samples using an appropriate analytical method and to assess whether cefuroxime administered provides concentrations above the MIC in both the blood and adipose tissue for all patients regardless of their BMI. Additionally, to assess whether there are differences in cefuroxime concentrations from obese vs non-obese women.

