### Participant selection and enrolment

Any patient (18–50 years) who requires a CS as part of their clinical care will be screened for inclusion. The potential participants will be identified using hospital clinical lists, where lists relate to a pre-booked CS a Good Clinical Practice (GCP) trained research midwife who is a member of the clinical care team will assess the eligibility of patients to participate in the study according to inclusion/exclusion criteria using screening form. The woman will then be provided with the participant information sheet at this meeting by the research midwife. In addition, if a pregnant woman is booked for CS at a meeting they may be informed about the study by a research midwife or their clinical care team and provided with a participant information sheet. The participants will receive information about the study well in advance (at prior clinic appointments) and at least 24 hours prior to CS so that all participants have sufficient time to consider taking part.

This study plans to compare data from obese (BMI ≥ 30 kg/m^2^) and non-obese women (BMI < 30 kg/m^2^) at the time of booking (10–14 weeks of pregnancy). At least 15 participants are required for each arm with a total of 30 participants. The study sequence is summarised in Table 2.

**Table 2 Tab2:** Summary of the C-LACE study sequence and methodology

Timing	Activity
Caesarean section booking clinic	Clinic list will be reviewed for eligible participants using the screening form
On the day of caesarean section	A Venflon cannula will be inserted into the woman as part of the research process to enable withdrawal of the required blood samples without the need for additional needles. This second access point will ensure that the blood sampling is minimally disruptive to the CS procedure.
At 30–40 days post-caesarean section	Participant’s medical file and notes will be reviewed by the research midwife to identify any post-surgical site infection which will be recorded on the 6-week outcome form. Research midwife will attempt to contact the participant 3 times between 30 and 40 days post-CS to complete the follow-up interview form.
Samples analysis	Blood and adipose tissue will be analysed by LC-MS/MS [15]

*GCP* Good Clinical Practice, *CS* Caesarean section, *LC-MS/MS* liquid Chromatography with tandem mass spectrometry

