### Statistics {20a}, sample size {14} and study assessment

There is no predefined sample size yet sufficient numbers are required to provide an estimate of average values as well as the level of inter-patient variability. Previous work to measure the concentration of antibiotics in plasma and in tissue in obese and non-obese pregnant women following CS has used sample sizes of 14 in each arm to detect differences in adipose antibiotic concentration [16, 17]. Therefore, in this study, we plan to recruit 15 women in each arm (BMI < 30 kg/m^2^ and BMI ≥ 30 kg/m^2^). The BMI measurements will be taken from the women at their time of booking appointment which occurs between 10 and 14 weeks of pregnancy. The BMI of participants immediately prior to CS will be determined to review any major changes during their pregnancy which may affect the results, for example, a change from < 30 kg/m^2^ to an extremely obese participant at CS.

The differences in mean concentration values in plasma and adipose tissue between the obese and non-obese populations will be compared using ANOVA analysis to determine whether there are significant differences. SPSS software will be used for all statistical analysis. The rate and type of infection will be analysed. The rate of infections will be analysed in correlation with (1) dose administered, (2) BMI and (3) cefuroxime concentrations at both sites at the time of skin incision and skin closure.

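### Fifteen women per arm is justified by estimation, but the obese versus non-obese comparison of cefuroxime levels is fixed as an ANOVA significance verdict for which the study was not sized (minor)

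*Protocol article*

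**What the plan says.** Three statements in the protocol article bear on this point.

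- **Purpose of the numbers.** The statistics and sample size section opens with "There is no predefined sample size yet sufficient numbers are required to provide an estimate of average values as well as the level of inter-patient" (the sentence ends by naming the spread between women). That is an estimation purpose, and the section says openly that no calculation lies behind the number.
- **Source of the number.** The section then cites earlier work that "has used sample sizes of 14 in each arm to detect differences in adipose antibiotic concentration", and concludes that "we plan to recruit 15 women in each arm". The participant selection section gives the same size: "At least 15 participants are required for each arm with a total of 30 participants".
- **Between-arm rule.** Mean concentrations in the two BMI groups "will be compared using ANOVA analysis to determine whether there are significant differences". The rule serves an objective placed last in the Objectives section: "Additionally, to assess whether there are differences in cefuroxime concentrations from obese vs non-obese women".

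The article states no alpha, SD, coefficient of variation or difference of interest for this comparison.

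**The concern.** The number of women and the analysis rule serve different purposes. A sample chosen to estimate averages and spread calls for an estimate of the group difference with its uncertainty. The article instead names a significance verdict, and supports the number with a precedent described in terms of detecting differences. A precedent for a sample size does not show power unless the SD and effect behind it are carried over, and here neither is.

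Two things are at stake. First, at this size a non-significant result is compatible with a sizeable true difference, so the verdict alone would say little. Second, the people planning the larger study need the size of the difference and how uncertain it is, and a significance verdict gives neither.

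**Working it through.** **Inputs from the article:** two groups, 15 women each, means compared by ANOVA. With two groups this is the two-sample t test.

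**Inputs assumed, because the article gives none:** two-sided alpha 0.05; standardised differences d of 0.3 to 1.2 SD; between-woman coefficient of variation (CV) of 20% to 60%; analysis on the log scale where a percentage difference is considered.

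**Plan's own figure.** The 15 per arm cannot be reproduced, since no alpha, power, effect or SD is stated. It is the precedent of 14, rounded up.

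**Step 1: power in SD units.** Degrees of freedom are 2 × 15 − 2 = 28, the critical t is 2.048, and the noncentrality is d × √(15/2) = 2.739 × d. The noncentral t distribution gives:

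| True difference (SD) | Noncentrality | Power | Missed |
|---|---|---|---|
| 0.3 | 0.82 | 12.5% | 87.5% |
| 0.5 | 1.37 | 26% | 74% |
| 0.74 | 2.03 | 50% | 50% |
| 0.8 | 2.19 | 56% | 44% |
| 1.0 | 2.74 | 75% | 25% |
| 1.06 | 2.90 | 80% | 20% |
| 1.2 | 3.29 | 89% | 11% |

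**Step 2: a true 25% lower concentration in obese women.** The log-scale SD is σ = √ln(1 + CV²), and d = −ln(0.75)/σ = 0.288/σ. The 95% CI for the ratio of geometric means multiplies and divides the estimate by exp(2.048 × σ × √(2/15)).

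| CV (assumed) | σ | d | Missed | 95% CI factor |
|---|---|---|---|---|
| 20% | 0.198 | 1.45 | 3% | ×/÷ 1.16 |
| 30% | 0.294 | 0.98 | 26% | ×/÷ 1.25 |
| 40% | 0.385 | 0.75 | 49% | ×/÷ 1.33 |
| 50% | 0.472 | 0.61 | 64% | ×/÷ 1.42 |
| 60% | 0.555 | 0.52 | 72% | ×/÷ 1.51 |

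**Step 3: where the balance tips.** Power passes 50% at 0.74 SD. That is a reduction of about 20% at CV 30%, 25% at CV 40% and 30% at CV 50%. Larger true reductions are detected more often than not.

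**Step 4: if samples are lost.** The feasibility criteria accept complete samples from 75% of each arm, and 0.75 × 15 = 11.25, so 12 women. With 12 per arm, power is 22% at 0.5 SD and 47% at 0.8 SD, and 80% power needs 1.20 SD. A single site and time may have more than 12 values, so this is the less favourable end.

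**Step 5: what an interval would add.** Suppose, for illustration, an observed ratio of 0.80 at CV 40%. The 95% CI runs from 0.80/1.33 = 0.60 to 0.80 × 1.33 = 1.06. A significance verdict would say only that no difference was shown. The interval shows that anything from 40% lower to slightly higher remains possible.

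**The case against.** The strongest case on the other side is that this is a pilot. Its main objective is feasibility, and all five success criteria are feasibility thresholds that do not use the ANOVA. The between-arm comparison is an additional objective, the article promises no power, and low power for such a comparison is to be expected. Confidence intervals and log transformation may stand in a full protocol or analysis plan that is not shown. All of this stands, and it is why the point is minor. What remains is the choice the article does state: a significance verdict, for a sample justified by estimation.

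Three stronger readings are tempting, and the article does not support them.

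- **A reader might infer that a relevant effect of obesity will usually be missed.** The article gives neither a CV nor a relevant difference. Over the ranges assumed here, power runs from about 12% to 97%, and differences above about 0.74 SD are found more often than not.
- **A reader might infer that a non-significant result will be reported as no difference.** No section says so. It could equally be reported as not shown or inconclusive. The wording leaves that misreading open but does not prescribe it.
- **A reader might infer that a missed difference would decide dosing.** The Background's aim to "suggest a dose adjustment if required and applicable" runs through the pharmacokinetic model fed by measured concentrations, and the abstract puts a larger study and a further trial in between. None of these steps is made to depend on the ANOVA p-value.

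**Conclusion.** The concern holds in a limited form. The article justifies 15 per arm by estimation but fixes a significance test as the only stated answer to the obese versus non-obese question on concentrations. At that size the test reaches 80% power only for a difference of about 1.06 SD. Moderate differences can often be missed: 74% of the time at 0.5 SD, and 26% to 72% of the time for a 25% reduction at CV 30% to 60%. A non-significant result could not support a statement that levels are similar.

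These figures rest on a two-sided alpha of 0.05, complete data in both arms, equal spread in the two groups and, for the percentage differences, log-normal concentrations with assumed CVs. The detectable difference in SD units does not depend on the CV. Severity is minor.

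**What to change.** In the statistics and sample size section:

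1. For each site (plasma, adipose tissue) and sampling time, make the obese/non-obese ratio of geometric mean concentrations with its 95% CI the main between-arm result. Any p-value becomes secondary.
2. State that a non-significant result is not evidence of similar levels.
3. Remove the implication that 14 or 15 per arm is enough to detect differences. State instead the expected precision (95% CI about ×/÷ 1.25 at CV 30% to ×/÷ 1.51 at CV 60%, with the CVs labelled as assumptions) or the detectable difference (about 1.06 SD at 80% power, two-sided alpha 0.05).

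No equivalence margin is needed unless the investigators intend to claim that there is no relevant difference. In that case the margin must be fixed before the analysis.

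The cost is a few sentences and one additional output per comparison, with no more women or samples. The downside is that some comparisons will be reported as inconclusive.

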#### Success criteria and assessment of C-LACE pilot and feasibility study

These criteria applied to participants consented and did not withdraw from the study at any time-point of C-LACE study:
Patients’ recruitment rate: as per Birmingham Women’s Hospital Caesarean Section rate, recruitment of 30 patients would be achievable easily within 3 months. If this was not achieved, the protocol (specific inclusion and exclusion criteria) would be reviewed and reassessed.Collecting samples: this pilot and feasibility study would be considered successful if plasma and adipose tissue samples at the time of incision and time of closure and plasma sample at time of recovery were successfully collected for ≥ 75% of participant in each arm. If this was not achievable, the sampling strategies will be revised and reassessed.Sample analysis: this pilot and feasibility study would be considered successful if ≥ 80% of plasma and adipose tissue samples collected were successfully analysed via the analytical method described; If not, sampling handling, transferring and sample analysis protocol will be revised and reassessed.Data collecting: this pilot and feasibility study would be considered successful if ≥ 80% of data collecting forms was fulfilled for each participant; if not, logistics and study procedure of C-LACE study will be revised at Birmingham Women’s Hospital.Follow-up: the described follow-up protocol will be considered successful if participants’ retention were ≥ 80%. The participant will be considered as lost to follow-up, if the participant could not be contacted and the patients file and notes were not reviewed.

Analysis and sub-analysis of outcomes and success criteria of C-LACE pilot and feasibility study will be made to explore the reasons of unsuccessful.

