### Withdrawal of study participants

Each participant has the right to withdraw from the study at any time and this will not affect their clinical care. In addition, the investigator may discontinue a participant from the study at any time if the investigator considers it necessary for any reason including the following:
Ineligibility (either arising during the study or retrospectively having been overlooked at screening)Withdrawal of consent

Withdrawal from the study will result in the exclusion of the data for that participant from analysis; provided that the withdrawal occurs within 3 months of data collection.

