### Missing data and lost to follow-up {20C}

Every attempt will be made to collect full follow-up data for all study participants; it is thus anticipated that missing data will be minimal. The main analysis will use available data only; however, the amount of missing data will be assessed, and if necessary, sensitivity analyses will be undertaken. If the participant could not be contacted, but the patients’ medical records and notes were reviewed, the participant will be considered enrolled in the follow-up. The patient will be considered as lost to follow-up, if the participant could not be contacted and the patients’ file and notes were not reviewed.

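### The retention (≥80%) and per-arm sampling (≥75%) success criteria leave out women who withdraw, so neither can register withdrawal of consent

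*Protocol article*

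**What the plan says.** All references are to the protocol article.

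- **Purpose.** Objectives {7} gives the main objective as assessing recruitment, sample collection, follow-up and study procedure. Outcomes {12} lists sample collection and retention among the feasibility outcomes.
- **Denominator.** The section on success criteria begins: "These criteria applied to participants consented and did not withdraw from the study at any time-point of C-LACE study". The five criteria follow under that sentence.
- **Sampling criterion.** Plasma and adipose samples at incision and closure must be obtained, and "plasma sample at time of recovery were successfully collected for ≥ 75% of participant in each arm".
- **Retention criterion.** "the described follow-up protocol will be considered successful if participants’ retention were ≥ 80" per cent.
- **Loss to follow-up.** "The participant will be considered as lost to follow-up, if the participant could not be contacted and the patients file and notes were not reviewed". Under Missing data and lost to follow-up {20C}, a woman who is not reached but whose notes are reviewed still counts: "the participant will be considered enrolled in the follow-up". Withdrawal appears in neither definition.
- **Routes out of the study.** Under Withdrawal of study participants, a woman may leave at any time, and "the investigator may discontinue a participant from the study at any time if the investigator considers it necessary for any reason", with late-discovered ineligibility given as one example. The same section says: "Withdrawal from the study will result in the exclusion of the data for that participant from analysis". That exclusion applies only if she withdraws no more than three months after the data were collected.
- **Numbers.** "At least 15 participants are required for each arm with a total of 30 participants". The recruitment criterion is 30 patients in 3 months.

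**The concern.** A retention percentage calculated only among women who did not withdraw excludes one of the main ways of not being retained. The definition of loss to follow-up does not bring it back. Among women who stay, a retention failure needs both no contact and no review of the notes.

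Withdrawal is informative in this study. Consent is signed at least 24 hours before surgery. The study then adds a second cannula, three blood samples and two adipose samples. A woman who withdraws consent because of those procedures is evidence about the sampling strategy that the pilot is meant to test, and the sampling criterion does not see her.

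The plan's responses (revising the sampling strategy, exploring why a criterion was missed) are tied to criteria that fail. Withdrawal would not trigger them through these two thresholds. The Abstract says the results will help develop a larger study, and its planners could take over a retention figure that leaves withdrawal out.

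**Working it through.** **The plan's own figures.** The thresholds are stipulated and the protocol says there is no predefined sample size, so no power or sample size calculation needs reproducing. With 30 women, 15 per arm and no withdrawals:

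- Retention: 0.80 × 30 = 24, so at least 24/30.
- Sampling: 0.75 × 15 = 11.25, so at least 12/15 per arm (11/15 = 73.3% falls short).

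**Two formulas.** Plan's rule: successes / (consented − withdrawn). Consented rule: successes / consented. The illustrations assume that every withdrawal is a withdrawal of consent by an eligible woman.

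**Retention, withdrawal the only loss, 30 consented.** The withdrawal counts are assumptions; the protocol gives no rate.

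| Withdrawn | Plan's rule | Consented rule |
|---|---|---|
| 0 | 30/30 = 100% | 30/30 = 100% |
| 6 | 24/24 = 100% | 24/30 = 80.0% (just met) |
| 7 | 23/23 = 100% | 23/30 = 76.7% (not met) |
| 10 | 20/20 = 100% | 20/30 = 66.7% |
| 15 | 15/15 = 100% | 15/30 = 50.0% |

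**Retention, withdrawal plus other losses.**

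- 10 withdraw, 2 of the other 20 are lost: 18/20 = 90% (met) against 18/30 = 60%.
- 10 withdraw, 4 of the other 20 are lost: 16/20 = 80% (still met) against 16/30 = 53.3%.

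**Sampling in one arm of 15, those withdrawn not sampled.**

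- 7 withdraw and 6 of the other 8 have the full set: 6/8 = 75% (met) against 6/15 = 40%.
- With withdrawal the only cause of failure, the consented rule is met at 3 withdrawals (12/15 = 80.0%) and missed at 4 (11/15 = 73.3%). The plan's rule gives 100% in both cases.

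A woman who withdraws after full sampling leaves both numerator and denominator. That can move the percentage slightly (12/15 = 80.0% becomes 11/14 = 78.6%), but she is still not counted as a failure.

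**How the consented rule would respond.** Binomial chance of meeting each criterion, withdrawal the only cause of failure, true withdrawal probability w assumed: P(X ≥ 24), X ~ Bin(30, 1 − w), for retention; [P(Y ≥ 12)]², Y ~ Bin(15, 1 − w), for sampling in both arms.

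| w | Retention met | Sampling met in both arms |
|---|---|---|
| 10% | 0.974 | 0.892 |
| 20% | 0.607 | 0.420 |
| 30% | 0.160 | 0.088 |
| 40% | 0.017 | 0.008 |

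Under the plan's rule and the same assumptions, both criteria are met at every w in the table, as long as some women remain in each arm.

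**The case against.** Several counter-arguments are sound and limit the point.

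- **The pilot as a whole.** A reader might infer that the pilot can be called successful at any withdrawal rate. The text does not support that. The opening restriction also covers recruitment, so if 30 consent and 10 withdraw, only 20 count towards the 30 in 3 months. That criterion fails unless further women are recruited in time, and no replacement rule is stated. Further recruitment could still hide the withdrawals.
- **Recruitment.** A reader might object that the recruitment criterion is a count and not a rate. Thirty women in 3 months is a rate over time. Consented over approached would be an additional statistic.
- **Refusing a procedure.** Declining the cannula or a sample is not withdrawal under the protocol. A woman who declines but stays in remains in the denominator and counts as a sampling failure. Both thresholds therefore still detect failures among women who stay.
- **Ineligibility after consent.** Eligibility is rechecked on the day of surgery. A woman who consents and then has an emergency section meets an exclusion criterion. Scoring her as not retained would push the figures down for a reason unrelated to acceptability.
- **Consequences.** A missed criterion leads to review and revision, and no stop/go decision is stated. The primary objective, cefuroxime concentration against the MIC, does not depend on these denominators. Nothing says that withdrawals will go unreported.

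None of this puts a woman who withdraws consent back into the retention or sampling criterion, and no other section does so.

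**Conclusion.** The point holds for withdrawal of consent and for two criteria: retention and per-arm sampling. As written, withdrawal is never a failure on either, although both measure named outcomes under the study's main objective. This is an explicit rule in the article, not a detail left to a fuller document.

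The actual size is unknown because no withdrawal rate is given. Starting from 15 consented per arm, and with no other losses, the rules would disagree from 7 withdrawals of 30 for retention, or from 4 in one arm for sampling if those women were not sampled. With fewer withdrawals the rules can still differ if some of the women who stay are also lost or not sampled. The figures of 10 of 30 and 7 of 15 are illustrations, not forecasts.

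A reader might also infer that the rule excluding withdrawn women's data must change. It need not. The denominator requires only how many women consented, how many withdrew and when, and whether the sample set had been collected. It requires none of their concentration or outcome data.

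**What to change.** In the success-criteria section:

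1. For sampling and retention, take as denominator all consented women who remain eligible at the day-of-surgery check. State that a woman who withdraws consent before that check stays in the denominator unless she is known to be ineligible.
2. Count withdrawal of consent as not retained and, where the sample set was not collected, as not sampled.
3. Report withdrawals of consent and post-consent ineligibility separately, by arm and time-point.
4. Leave the sample-analysis criterion as it is, since its denominator is samples collected. Leave the data-exclusion rule under Withdrawal of study participants unchanged. Altering that rule would change data handling in a protocol already approved by HRA and HCRW, and this point does not need it.

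The cost is a change of wording and a tally of withdrawals. The retention and sampling percentages may be less favourable.

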### Patient consent {26a}

A suitably qualified research midwife or doctor who is also part of the clinical care team will introduce the study to the woman at their pre-operative assessment. A participant information sheet (PIS) will be provided to facilitate this process. Investigators will ensure that they adequately explain the aim, anticipated benefits and potential hazards of taking part in the trial to the woman. They will also stress that participation is voluntary and that the woman is free to refuse to take part and may withdraw from the trial at any time. The woman will be given adequate time to read the PIS and to discuss their potential participation and be given the opportunity to ask questions. If the woman expresses an interest in participating in the trial, they will be asked to sign and date the latest version of the informed consent form at least 24 h prior to CS. The woman will be asked for her consent to withdraw 3 blood samples (with a maximum volume of 10 mL blood per sample) and 2 fat tissues and for collection of outcome data from their medical records and a telephone interview at 30–40 days post-natal that will take approximately 5–15 min.

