#### Part A: Sample collection at caesarean section

The clinical care team will record the time of cefuroxime administration, dose administered, type of anaesthesia used, blood loss and other relevant clinical information. Five samples will be collected: 1 blood sample at time of skin incision, 1 blood sample at time of skin closure, 1 blood sample at recovery room (< 3 h following CS), 1 adipose tissue sample (approximately 1 cm from the skin in the middle of the Pfannesnstiel or vertical midline incision) at skin incision and one adipose tissue sample (from a similar location to sample 1) just prior to skin closure.

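### The ≥ 80% sample-analysis criterion pools plasma with adipose tissue and both arms, so it can be met while half of all adipose assays fail

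*Protocol article*

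**What the plan says.** All references are to the Protocol article. The section *Success criteria and assessment of C-LACE pilot and feasibility study* lists five criteria, each with its own corrective step. Three matter here.

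- **Recruitment.** The target is a total: "recruitment of 30 patients would be achievable easily within 3 months".
- **Collection.** A full set of samples must be "successfully collected for ≥ 75% of participant in each arm".
- **Analysis.** The pilot is "successful if ≥ 80% of plasma and adipose tissue samples collected were successfully analysed via the analytical method described". If it is not, handling, transport and assay procedures are to be revised.

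The same section limits the population: "These criteria applied to participants consented and did not withdraw from the study at any time-point".

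The counts come from elsewhere. *Participant selection and enrolment* states: "At least 15 participants are required for each arm with a total of 30 participants". Under *Patient consent*, each woman agrees to let the team "withdraw 3 blood samples (with a maximum volume of 10 mL blood per sample) and 2 fat tissues", and *Part A: Sample collection at caesarean section* gives the same five samples.

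The *Objectives* section makes it primary to measure cefuroxime in blood and tissue and to judge it against the MIC in both, whatever the woman's BMI. The *Statistics* section compares mean plasma and adipose concentrations between obese and non-obese women by ANOVA.

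**The concern.** The collection criterion is split by arm and the analysis criterion next to it is not. Collection does not protect against assay failure: a sample that is taken but cannot be measured still counts as collected. The recruitment, forms and follow-up criteria do not test assay success either. The pooled percentage is therefore the only check on whether the assay worked.

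Plasma makes up three of every five samples, so good plasma results can offset poor adipose results. Adipose tissue is the matrix on which half of the primary objective rests, and obese women are the group the study was set up to learn about. If adipose failures were offset in this way, the criterion would be met and the revision attached to it would not be called for before the larger study. The closing sentence of the section provides for exploring reasons for lack of success, so a pooled pass need not set that in motion.

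**Working it through.** **Inputs.** 15 women per arm and 30 in total (*Participant selection and enrolment*); 3 blood and 2 adipose samples per woman (*Patient consent*; *Part A*); threshold 80% of samples collected (*Success criteria*). The protocol gives no power calculation, and none is needed for a count.

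**Reproducing the plan's counts.** 2 × 15 = 30 women and 3 + 2 = 5 samples each, as stated.

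**Planned samples.**
- All samples: 30 × 5 = 150
- Plasma: 30 × 3 = 90
- Adipose: 30 × 2 = 60, of which 15 × 2 = 30 come from the obese arm
- Needed to pass: 0.80 × 150 = 120, so 30 failures are tolerated

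**Pooled criterion at full collection.**

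| Assay failures | Analysed | Rate | Result |
|---|---|---|---|
| Any 30 of the 60 adipose | 120/150 | 80.0% | met |
| All 30 obese-arm adipose (a special case of the row above) | 120/150 | 80.0% | met |
| Those 30 and one more | 119/150 | 79.3% | missed |
| All 60 adipose | 90/150 | 60.0% | missed |

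**Incomplete collection (assumed patterns).** The collection criterion allows ceil(0.75 × 15) = 12 complete women per arm. Suppose every obese-arm adipose sample that was collected fails and all else is analysed.

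- Three obese women lack only their adipose samples: 150 − 6 = 144 collected, 24 fail, 120/144 = 83.3%, met. The threshold needs 116 (0.80 × 144 = 115.2), so four more failures are tolerated.
- Three obese women give no samples: 135 collected, 24 fail, 111/135 = 82.2%, met.
- Three women in each arm give none: 120 collected, 24 fail, 96/120 = 80.0%, met.
- Three non-obese women give none: 135 collected, 30 fail, 105/135 = 77.8%, missed.

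**Possible splits at full collection.**

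- By matrix only: adipose needs 0.80 × 60 = 48, so 12 may fail. Losing all obese-arm adipose gives 30/60 = 50% and is caught, but 12 failures all in obese women would leave 18/30 = 60% of theirs and pass.
- By arm only: each arm needs 0.80 × 75 = 60, so 15 may fail. Losing all obese-arm adipose gives 45/75 = 60% and is caught, but 15 failures all in adipose would leave 15/30 = 50% and pass.
- By matrix within arm: plasma needs 0.80 × 45 = 36 and adipose 0.80 × 30 = 24 in each arm. Losing all obese-arm adipose gives 0/30 and is caught. Failures tolerated are 9 + 6 = 15 per arm, or 30 in total, the same total as now but no longer free to gather in one cell.

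**The case against.** **The extreme case is a boundary point.** At full collection it needs every other sample to be analysed. One analytical method is named for both arms, and nothing in the protocol suggests it would fail on all obese adipose tissue and work on all non-obese. A general failure of the adipose assay is caught at 60%. This stands, and it limits the severity. It does not remove the point, because the same 80.0% arises from any pattern of 30 adipose failures, and some collection shortfalls leave room for more.

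**The wording could mean 80% of each matrix.** On that reading, losing all obese-arm adipose results gives 50% and fails. The text does not say so, and the adjacent criterion spells out its split. An ambiguity in a decision rule calls for the same correction.

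**The gap would be noticed anyway.** A reader might infer that the pilot could be declared a success with nobody aware that obese adipose data were missing. The documents do not support that. The ANOVA would expose an empty cell, and *Missing data and lost to follow-up* says the amount of missing data will be assessed. What remains is that the criterion itself would not call for the corrective step.

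**Recruitment is already planned by arm.** This is correct: two other sections give 15 per arm, and 30 is their sum. A reader might take the 16% obesity figure in the *Background* to mean that few obese women would be enrolled. That does not follow, because women are screened from clinic lists into BMI-defined groups and the number of caesarean sections at the hospital is not given. Only the wording of the criterion needs to match.

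**Conclusion.** The point holds as a weakness in one stated feasibility rule. At 15 + 15 women and full collection, the criterion is met with up to 30 of 60 adipose assays failing, in any distribution between the arms, provided all plasma is analysed. This rests on the pooled reading of the sentence and on no withdrawals altering the 150 samples. The severity is minor to moderate: no confirmatory decision depends on the rule, and the extreme case has no slack at full collection.

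Two further inferences should not be drawn.

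- A reader might multiply the thresholds, 12 × 0.8 = 9.6, and conclude that 9 to 10 women per arm are assured. The 80% applies to samples, not women. One failed adipose sample in each of the 30 women also gives 120/150 = 80.0% and leaves no woman with a complete set. Complete sets are not required for analysis either, since the main analysis uses available data.
- A reader might compare such numbers with the earlier work that "has used sample sizes of 14 in each arm to detect differences in adipose antibiotic concentration" and infer a loss of power. The protocol states that it has no predefined sample size and aims to estimate averages and inter-patient variability, so it makes no power claim that could be eroded.

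**What to change.** In *Success criteria*, state that at least 80% of the plasma samples collected and at least 80% of the adipose samples collected must be successfully analysed, each within each arm. At full collection this means at least 36/45 plasma and 24/30 adipose per arm. Attach the existing corrective step to failure of any of the four.

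In the same section, word the recruitment criterion as 15 women per arm (30 in total) within three months, to agree with *Participant selection and enrolment* and *Statistics*.

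The cost is a change of wording, with no additional women, samples or procedures. The analysis criterion becomes slightly harder to meet, because four proportions on small denominators must each reach 80%.
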